## Abstract

**Background:**

Reducing alcohol related harms in Australian Defence Force (ADF) trainees has been identified as a priority, but there are few evidence-based prevention programs available for the military setting. The study aims to test whether the P.A.R.T.Y. program delivered in-hospital or on-base, can reduce harmful alcohol consumption among ADF trainees.

**Methods/design:**

The study is a 3-arm randomized controlled trial, involving 953 Royal Australian Navy trainees from a single base. Trainees, aged 18 to 30 years, will be randomly assigned to the study arms: i. in-hospital P.A.R.T.Y.; ii. On-base P.A.R.T.Y.; and iii. Control group. All groups will receive the routine ADF annual alcohol awareness training. The primary outcome is the proportion of participants reporting an Alcohol Use Disorders Identification Test (AUDIT) score of 8 or above at 12 months’ post-intervention. The secondary outcome is the number of alcohol related incidents reported to the Royal Australian Navy (RAN) in the 12 months’ post-intervention.

**Discussion:**

This is the first trial of the use of the P.A.R.T.Y. program in the military. If the proposed intervention proves efficacious, it may be a useful program in the early education of RAN trainees.

**Trial registration:**

Australian New Zealand Clinical Trials Registry (ANZCTR): ACTRN12614001332617, date of registration: 18/12/2014 ‘retrospectively registered’.

**Electronic supplementary material:**

The online version of this article (doi:10.1186/s12889-017-4330-8) contains supplementary material, which is available to authorized users.

## Background

Almost all societies that consume alcohol experience related health and social problems [1]. Excessive alcohol consumption, and associated harm, is a major contributor to morbidity and mortality in Australia and other developed countries [1–3]. Therefore, interventions to reduce excessive consumption and associated harm are needed.

To reduce the occurrence and cost of substance abuse problems, it is important to intervene early before harmful patterns of substance use are established [4, 5]. One intervention that is commonly used in an effort to reduce alcohol related harm in young people is the P.A.R.T.Y. program. P.A.R.T.Y. is an in-hospital, injury awareness and prevention program which originated in Canada in 1986, and now operates in over 100 sites around the world.

P.A.R.T.Y. is a full day program that involves interaction, generally of school groups, with emergency services personnel, health professionals, and patients who have experienced trauma and survived. Holding the program within a hospital environment is expected to leave a significant and lasting impression of the consequences of preventable trauma and risk taking behaviours [6, 7] (Additional file 1: Appendixes 1 and 2).

Case-control studies have shown that attendance at P.A.R.T.Y. reduced major trauma presentations in senior school students in Canada [6], and recidivism in juvenile justice young offenders [7]. Further, a pilot cohort study explored the feasibility of delivering the P.A.R.T.Y. program to 108 ‘at risk’ naval trainees, and found that 12 months after program participation, 14% of participants had been reported for an alcohol related incident, with the rate of reported alcohol related incidents following the program higher for participants who had a pre-program incident on record ([name], [name], [name], [name] and [name]: Piloting an injury awareness and education program for reducing alcohol related harm in Navy Trainees, Submitted).

While these observational studies provide promising supporting evidence for P.A.R.T.Y., the efficacy of this program in reducing risk taking behaviour and alcohol related harms has not been established. Our study will test whether participation in either an in-hospital or on-base version of the P.A.R.T.Y. program leads to a reduction in prevalence of risky drinking (hazardous/harmful, measured using the Alcohol Use Disorders Identification Test, AUDIT) [8–10] at 12 months’ post-intervention in a randomised controlled trial (RCT). We expect that naval trainees who participate in an on-base, or in-hospital, P.A.R.T.Y program will have a lower prevalence of hazardous or harmful drinking behaviour, compared to naval trainees who do not attend the P.A.R.T.Y. program.

## Methods

### Setting

Participants for this study will be recruited from Initial Entry Trainees who are completing their specialist training at the RAN’s key training establishment in Victoria. The intervention (P.A.R.T.Y.) will be delivered at two settings; at The Alfred (‘in-hospital’) and at the participating naval base (‘on-base’).

### Ethics approval and trial registration

Ethical approval for the study was obtained from the Australian Defence (739–13), Alfred Health (155/16) and Monash University (CF14/1667–2,014,000,783) Human Research Ethics Committees. The trial is registered in the Australian New Zealand Clinical Trials Registry (ANZCTR) ACTRN12614001332617.

### Study design

In this non-blinded RCT, participants will be randomised to one of three arms:i.In-hospital P.A.R.T.Y. program and annual alcohol and other drugs awareness training;ii.On-Base P.A.R.T.Y. program and annual alcohol and other drugs awareness training; andiii.Annual alcohol and other drugs awareness training only (Fig. 1).

**Fig. 1 Fig1:**
[figure not shown]
Participant flow chart (AUDIT, Alcohol Use Disorders Identification Test; MDMQ-R, Modified Drinking Motives Questionnaire – Revised; P.A.R.T.Y. Defence A&BQ, Prevent Alcohol and Risk-related Trauma in Youth Defence Attitudes and Behaviours Questionnaires)

### Participants and procedure

#### Inclusion and exclusion criteria

Naval trainees will be eligible for inclusion in the study if they meet the following criteria:i.Stationed at the participating naval base for training of at least 12 weeks’ duration following initial entry training (IET), and;ii.No alcohol related incident on their service record since joining the RAN.

### Procedures

#### Screening

Participants will be recruited from all initial entry trainees based at the participating naval base. The recruitment process is scheduled from March 2014 to May 2016 and will be conducted by the research project staff. Eligible participants will be provided with a baseline screening pack which includes a participant information and consent form, a copy of the Australian Defence Human Research Ethics Committee – Guidelines for Volunteers information sheet, a demographics form, and three screening questionnaires:i.Alcohol Use Disorders Identification Test (AUDIT) is a 10-item questionnaire validated in a cross-national study initiated by the World Health Organization (WHO) in 1982 [10]. AUDIT is used to screen for hazardous and harmful drinking, with scores ≥8 typically taken to indicate hazardous or harmful drinking [10–12].ii.Modified Drinking Motives Questionnaire – Revised (MDMQ-R), first conceptualised in 1988 [13] to describe the motivators for the use of alcohol. The MDMQ-R consists of 28 items, each of these contribute to one of five subscales: social, coping-anxiety, coping-depression, enhancement and conformity; andiii.P.A.R.T.Y. Defence Attitudes and Behaviours Questionnaire, developed specifically for this study comprising questions stemming from both the annual alcohol poll conducted by the Foundation for Alcohol Research and Education (FARE) and recommendations from the review of the use of alcohol in the Australian Defence Force (ADF) Additional file 1: Appendix 1 [14, 15].

#### Randomisation

Following completion of consent forms and baseline screening measures, consented participants will be randomly allocated in a 1:1:1 ratio to one of the three trial arms. Randomisation will be stratified by gender in block sizes of 3, 6, 9, 12 or 15 patients. Randomisation will take place at an individual level. The allocation will be performed by a designated person not involved in the conduct of the programs, measurement of the outcomes, or analysis of the data. An opaque envelope containing computer-generated (RALLOC, Stata12) random intervention allocation will be provided for each participant.

#### Blinding

Given the nature of the intervention, it is not feasible to blind the participants to their group assignment. However, the P.A.R.T.Y. programs will be delivered independent of the research team, limiting the potential for the study to influence program content and conduct. Project personnel involved in randomisation will not participate in collection of outcomes data for the study cohort, conversely the personnel involved in collecting baseline and 12 month follow up data will not be involved in the randomisation of participants.

### Sample-size calculation

Similar studies have not previously been conducted in the ADF setting. Therefore, we based the effect-size on unpublished data provided on request from the RAN summarising the AUDIT scores and alcohol incident rates of RAN personnel. Published data show 1 in 5 (20%) ADF personnel report an AUDIT score of 8 or above, which represents hazardous or harmful alcohol consumption behaviour [15]. Our study was powered to detect an 8% lower prevalence of moderate to high risk behaviour (AUDIT score 8+) in the intervention groups relative to the control group with 80% power. To achieve this, 284 participants in each group is needed and this will be increased to 310 per group to allow for a 10% loss to follow-up.

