#### Data analysis

Data will be analysed on a per-protocol and intention to treat basis. Summary statistics will be used to describe the difference between groups and ascertain if balance of groups has been achieved through the randomisation process. Frequencies and percentages will be used for categorical variables and mean and standard deviations, or median and inter-quartile range for continuous variables.

The primary outcome will be analysed using a modified Poisson regression model with a robust variable estimator [16]. The relative risk, and 95% confidence intervals (CI) of reporting an AUDIT score of 8 or above in the intervention groups will be calculated relative to the control group. Where necessary, the model will be adjusted for factors not balanced between the groups through the randomisation process.

The secondary outcome will be analysed using a Cox Proportional Hazards regression model assessing time to an alcohol related incident reported to the RAN, with participants not reported for an alcohol related incident censored at 12 months’ post-intervention. Where a participant leaves the RAN, these participants will be censored at the date of discharge from the RAN [16–18]. Hazard ratios, and 95% CI will be reported. For both analyses, multivariate models will be used if there is baseline imbalance between the groups.

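### The 284 per group follows from 20% v 12% only as a one-sided 5% calculation; under the planned two-sided 95% intervals, power is about 74%, not 80%

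*Protocol article*

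**What the plan says.** The Sample-size calculation section of the protocol article gives one prevalence for the primary endpoint: "Published data show 1 in 5 (20%) ADF personnel report an AUDIT score of 8 or above". The trial is described as "powered to detect an 8% lower prevalence of moderate to high risk behaviour (AUDIT score 8+) in the intervention groups relative to the control group"; the power claimed is 80%. The result is "To achieve this, 284 participants in each group is needed". Attrition is then handled by inflating that number: "this will be increased to 310 per group to allow for a 10% loss to follow-up". Neither the significance level nor the sidedness is printed there.

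Participants are "randomly allocated in a 1:1:1 ratio to one of the three trial arms" (Randomisation), and the abstract gives a total of 953.

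Under Data analysis, the primary outcome is analysed by modified Poisson regression, reporting "The relative risk, and 95% confidence intervals (CI) of reporting an AUDIT score of 8 or above" for the intervention groups relative to control. The Background says the authors expect that trainees in either program "will have a lower prevalence of hazardous or harmful drinking behaviour". That is a directional expectation, but no section declares a one-sided test.

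**The concern.** The printed inputs, the printed sample size and the printed analysis do not agree with one another. A 95% confidence interval for the relative risk that excludes 1 is a two-sided 5% test. At 20% v 12%, 284 per group is too few for 80% power on that test, and it is the exact answer to a different, one-sided calculation.

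This concerns the primary comparison of a trial meant to inform further roll-out of the program. If the result is inconclusive and is read against a claimed 80% power, the evidence against an 8-point reduction will look stronger than the design supports.

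**Working it through.** **Inputs.** Control proportion p1 = 0.20, difference 0.08 so p2 = 0.12, power 80% (z = 0.8416), all from Sample-size calculation. Equal allocation is from Randomisation. The two-sided 5% level (z = 1.960) is inferred from the 95% intervals in Data analysis; the one-sided 5% value is z = 1.645.

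**Formula.** For two proportions, with p̄ = (p1 + p2)/2 = 0.16:

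n = [z_α √(2p̄(1−p̄)) + z_β √(p1(1−p1) + p2(1−p2))]² / (p1−p2)²

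Here √(2 × 0.16 × 0.84) = 0.5185 and √(0.16 + 0.1056) = 0.5154. The continuity-corrected size is n_c = (n/4)[1 + √(1 + 4/(n|p1−p2|))]².

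**Step 1: reproduce 284.** One-sided 5%: (1.645 × 0.5185 + 0.8416 × 0.5154)² / 0.0064 = (0.8528 + 0.4337)² / 0.0064 = 258.6, so 259. With continuity correction: 283.07, so **284**. The printed figure is matched exactly.

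**Step 2: the same inputs, two-sided 5%.** (1.0162 + 0.4337)² / 0.0064 = 328.5, so **329**. With continuity correction: 353.03, so **354**.

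**Step 3: is there another route to 284?**

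| Method, 20% v 12%, 80% power | One-sided 5% | Two-sided 5% |
|---|---|---|
| Pooled variance, no correction | 259 | 329 |
| Pooled variance, continuity correction | **284** | 354 |
| Unpooled variance | 257 | 326 |
| Arcsine | 256 | 325 |
| Log relative risk | 269 | 341 |

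No two-sided version comes close. Reading the difference as 28% v 20% gives 352 to 471 with the pooled formula across sidedness and correction. Reading it as a relative 8% reduction (20% v 18.4%) gives more than 7,000. Neither fits.

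**Step 4: two-sided power at the sizes in the document.** Power = Φ{[0.08 − 1.960 √(2p̄(1−p̄)/n)] / √((p1(1−p1) + p2(1−p2))/n)}. At n = 284 this is Φ[(0.08 − 1.960 × 0.03076)/0.03058] = Φ(0.644) = 74.0%.

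| Analysed per group | Source | Two-sided 5% power |
|---|---|---|
| 279 | 310 × 0.9 | 73.3% |
| 284 | stated requirement | 74.0% |
| 286 | 953/3 × 0.9 = 285.9 | 74.3% |
| 310 | 310 with no loss | 77.7% |
| 318 | 953/3 with no loss | 78.7% |

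**Step 5: does the result depend on the approximation?** At 284 per group, exact enumeration of the binomial outcomes gives 74.6% for the two-sided z test and 74.0% for a Wald test on the log relative risk, which is close to the planned analysis. The normal approximation on the log relative risk gives 72.5%. With continuity correction, the basis on which 284 itself was obtained, power is 70.2%.

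**Step 6: detectable difference.** With 286 per group, two-sided 5%, 20% v 11.5% gives 79.8% power. The difference detectable at 80% power is therefore about 8.5 points, not 8.

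**Step 7: control rates that would rescue 284 two-sided.** Keeping the 8-point difference, about 17.4% v 9.4% gives 284 without correction, and about 16.1% v 8.1% gives it with correction (16% v 8% gives 283).

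**The case against.** The strongest reply is that the section does not say outright that 20% was the control rate in the calculation. It says the effect size rested on unpublished Navy data, and gives the 20% separately as a published figure for all Defence personnel. The trial enrols recent entrants with no alcohol incident on record, so a lower rate is plausible, and step 7 shows that one near 16% or 17% would make 284 a correct two-sided figure. This stands in part: the 74% is conditional on 20%, and the one-sided origin is an inference. But no other rate is printed, and the exact match at 20% v 12% makes the one-sided reading the likelier one. If another rate was used, the paragraph still sets 284 beside a prevalence that did not produce it.

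It can also be said that an article may leave alpha and sidedness to the full protocol. That is accepted, and their omission is not the point. At 20% v 12%, no such detail can make 284 deliver 80% power for a two-sided 5% analysis. A one-sided design could be defended from the directional expectation in the Background, but only if it were declared and carried into the analysis, and the article reports 95% intervals.

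Finally, the shift from 8 to 8.5 points is modest, and readers can judge an inconclusive result from the interval, whose width does not depend on the planning power. Both are true and limit the practical harm. They do not make the stated power correct.

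**Conclusion.** The concern holds. On the only inputs printed, the stated sample size does not give the stated power under the analysis the article describes. The two-sided requirement is 329 per group (354 corrected), so 284 is 45 short, which is 45/284 = 16% of the stated figure. Two-sided power is about 74% at 284 to 286 analysed per group, a type II risk of about 26% instead of 20%. It stays below 80% at every enrolment figure in the document, including all 953 with no loss.

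This rests on a 20% control prevalence, an absolute difference of 8 points, and the 95% interval as the two-sided 5% criterion. The arithmetic is certain given these. That 284 came from a one-sided, continuity-corrected calculation is inferred from the exact match.

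**What to change.** Rewrite the sample-size paragraph so that its inputs, size and power agree with the Data analysis section. If 20% was the control rate, state: two-sided 5%, 20% v 12%, power about 74% with 284 to 286 analysed per group, and a detectable difference of about 8.5 points (20% v 11.5%) at 80% power. Say whether a continuity correction was used; with it, power at 284 is about 70%. If another control rate was used, state it and its source and reconcile it with the 20% now printed.

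Do not move the primary analysis to a one-sided 5% test to preserve the 80% figure.

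The cost is wording only: no extra participants and no change to the outcome or model. The stated power becomes less favourable.

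### The enrolment target of 310 per group leaves 279 after the stated 10% loss, 5 short of the required 284; retaining 284 needs 316 per group

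*Protocol article*

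**What the plan says.** The Sample-size calculation section of the protocol article gives the full chain of planning figures:

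- Background prevalence: "Published data show 1 in 5 (20%) ADF personnel report an AUDIT score of 8 or above".
- Effect to be detected: "powered to detect an 8% lower prevalence of moderate to high risk behaviour (AUDIT score 8+) in the intervention groups relative to the control group".
- Power: 80%.
- Evaluable number: "284 participants in each group is needed".
- Attrition allowance: "this will be increased to 310 per group to allow for a 10% loss to follow-up".

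Under Randomisation, participants are "randomly allocated in a 1:1:1 ratio to one of the three trial arms", so 310 per group implies 930 in total. The abstract's Methods/design paragraph describes a trial "involving 953 Royal Australian Navy trainees from a single base". It does not call 953 a target or an enrolment count.

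**The concern.** An allowance for loss has one job: the number left after the assumed loss should be at least the evaluable number. Here the requirement, the loss rate and the inflated target appear side by side, and the target fails that test. The primary outcome is a self-reported AUDIT score at 12 months, so participants lost before then reduce the number analysed. If 310 per group were enrolled and 10% were lost as assumed, the trial would finish below the number it says it needs. A reader also meets a second total, 953, with nothing to say how it relates to 3 × 310.

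**Working it through.** **Inputs.** From Sample-size calculation: 20% prevalence, 8% lower in the intervention groups, 80% power, 284 evaluable per group, 310 enrolled per group, 10% loss. From Randomisation: three arms, 1:1:1. From the abstract: 953. Assumed, because the article does not state them: alpha 0.05, tried one-sided and two-sided, with and without continuity correction. The 8% is read as percentage points (20% v 12%). Read as a relative reduction (20% v 18.4%), the requirement would be at least 7,493 per group, which cannot be what was meant.

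**Step 1: reproduce 284.** For two proportions with mean 0.16 and difference d = 0.08:

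n = [z_α √(2 × 0.16 × 0.84) + z_β √(0.20 × 0.80 + 0.12 × 0.88)]² / 0.08²

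The continuity-corrected number is (n/4) × [1 + √(1 + 4/(n d))]².

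| Basis (5%, 80% power) | n per group |
|---|---|
| One-sided, uncorrected | 259 |
| One-sided, continuity-corrected | **284** |
| Two-sided, uncorrected | 329 |
| Two-sided, continuity-corrected | 354 |

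Of these four, only the one-sided corrected version gives the article's figure.

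**Step 2: inflate for loss.**

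- Correct method: 284 / (1 − 0.10) = 315.6, so 316 per group; 3 × 316 = 948.
- Common shortcut: 284 × 1.10 = 312.4, so 313 per group; 3 × 313 = 939.
- Stated: 310 per group; 3 × 310 = 930.

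Neither method gives 310. It is 6 short of 316 (1.9%) and 3 short of 313.

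**Step 3: test the stated target.**

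- Remaining after 10% loss: 310 × 0.90 = 279; 284 − 279 = 5 short per group.
- Largest loss that still leaves 284: 1 − 284/310 = 8.4%.

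**Step 4: cost in power, 20% v 12%.**

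| Basis (5%) | at 284 | at 279 | Loss |
|---|---|---|---|
| One-sided, continuity-corrected | 80.1% | 79.4% | 0.7 points |
| Two-sided, uncorrected | 74.0% | 73.3% | 0.7 points |

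**Step 5: the figure in the abstract.**

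- 953/3 = 317.7 per group; 317.7 × 0.90 = 285.9, about 286, which is above 284.
- 953 − 930 = 23; 953 − 948 = 5.

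**The case against.** The strongest defence is that this is a rounding-sized slip with almost no consequence. The gap is 5 evaluable participants per group, the 10% is itself a planning guess, and 310 already tolerates 8.4%. If 953 trainees were enrolled, the evaluable number is met even after 10% loss. All of that stands, and it limits the weight of the point. It does not make the published sentence correct: 279 is below 284, and no unseen analysis plan can change that.

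Three stronger readings are tempting, and the article does not support them.

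- *The slip costs the trial about 7 points of power.* A reader might set 73.3% at 279 (two-sided, uncorrected) against the 80% claimed. On that same basis 284 gives only 74.0%, so nearly all of the gap comes from how 284 was obtained and very little from the attrition allowance.
- *Enrolling 316 restores 80% on any basis.* It restores 284 evaluable per group. That is 80.1% power on the one-sided corrected basis, but still 74.0% two-sided and uncorrected.
- *The totals of 930 and 953 contradict each other.* 930 follows from a planning requirement, while 953 is not labelled. Recruitment was scheduled to end in May 2016 and the article's DOI contains 017, which suggests publication after that, so 953 may be the number enrolled. That is an inference; the article does not say. A target and an enrolment count may differ without error, and an enrolment count needs no derivation. The fair request is to label the figure.

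**Conclusion.** The attrition sentence is wrong as written: 310 per group does not preserve 284 after 10% loss. The shortfall is 5 evaluable per group against the stated need, or 6 enrolled per group against the correct 316. This conclusion uses only the article's own 284, 310 and 10%, and no outside assumption. The size of the effect, about 0.7 points of power, rests on 20% v 12% and an assumed 5% alpha, and is nearly the same one-sided or two-sided. It is a minor arithmetic error that should be corrected; it does not by itself undermine the trial's power. A conflict between 930 and 953 is not established; what is established is that the article does not say what 953 represents.

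**What to change.** In Sample-size calculation, make one of two changes:

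- restate the target as 316 per group (948 in total) to retain 284 per group after 10% loss; or
- keep 310 and state that it allows for about 8% loss.

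In the abstract, say whether 953 is a target or the number enrolled. If it is the number enrolled, it can stand beside a different planning total, and the text can note that it leaves about 286 per group after 10% loss. If it is a target, give its derivation and use the same total in both places.

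The cost is a sentence or two of wording. Since 953 exceeds 948, no extra recruitment follows, and no analysis changes.
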